## Methods

### Participants

Children (aged 2-7 years) and their parents will be referred through community channels after seeking help or support. The research will be conducted in clinical practice in the Netherlands, where families first follow a standard intake procedure (which includes an intake interview, completion of a set of questionnaires, and being referred to the right area of expertise) to establish their need for help. After this, families can be included in the study and receive PCIT-VR if the following criteria are met:

Disruptive behavior problems of the child are a reason for referralChildren are aged between 2 and 7 yearsParents speak Dutch or English

A total of 15 families will be included, preferably those who finish the treatment (including all treatment phases and measurement points).

As the design is a SCED, the calculations for the number of participants are based on the What Works Clearinghouse (WWC) [40] and information gained from previous PCIT research. The WWC standards dictate that there are 5 criteria that should be acknowledged in a SCED. One of these criteria states that the minimum number of participants necessary to demonstrate an intervention effect is 3 [41]. In addition, the American Psychological Association [42] states that to display the effectiveness of an intervention, a minimum of 9 replicated single-case studies should be performed. Furthermore, attrition rates according to the standard PCIT ranged between 34% and 77% [43]. Specifically, in the Netherlands, a previous study showed a 40% attrition rate [19]. Therefore, this study will strive to include 15 families, preferably those who finish the entire trajectory to (1) adhere to a minimum of 3 participants according to WWC standards, (2) be able to state that the intervention is effective in accordance with the American Psychological Association guidelines, and (3) compensate for the potential of a 40% attrition rate.

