Secondary objectives are the effects that we expect because of the overall amelioration of positive parenting skills that cause both parental stress and child disruptive behavior to diminish. Therefore, we expect that the total number of PCIT sessions will diminish and that the overall completion of treatment will increase. In addition, family dynamics and competencies will be secondarily measured, meaning that we will be able to evaluate parental compliance in the use of VR and evaluate potential risk factors for dropout. We believe that parents choosing to use VR will show higher levels of compliance as they want to use an additional tool to learn the skills. Secondary objectives also include positive VR experiences and general therapy satisfaction. Furthermore, we expect that PCIT-VR will secondarily lead to a better quality of parent-child relationships. We expect that the effects of PCIT-VR are further maintained and engrained in the long term because of the additional skill training provided by the VR scenarios.

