### Inclusion Criteria

Families that are referred for treatment to the clinical practice will be screened using a questionnaire for behavioral problems, the Eyberg Child Behavior Inventory (ECBI) [44] and a questionnaire about parental stress (*opvoedingsbelasting vragenlijst* [OBVL]; in Dutch) [45]. All families that are referred will be required to fill out both questionnaires on the web, where their scores are checked to see whether they meet the inclusion criteria. The clinical cutoff score for the ECBI is >131 according to US norms, meaning that all scores >131 will be included [46]. For OBVL, a T score of ≥60 is considered problematic or even clinical, thus counting as the cutoff score.

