The multiple baseline SCED in this study is set up as shown in Figure 1. First, informed consent will be signed after families have received verbal and written information about the study. Second, participants will be dually randomized (by an external party) to determine their baseline period (4, 5, or 6 weeks of baseline measurements; phase A) and the addition of their VR element (VR at the start of CDI and after 3 or 6 sessions of CDI; phase B). After randomization, participants will start with phase A—the baseline period. Parents will electronically fill out the questionnaires weekly regarding child disruptive behaviors and parental stress using the ECBI and the short version of the OBVL. At the end of phase A, a pretreatment assessment will be performed. In this assessment, parents will be required to electronically fill out more questionnaires regarding both child and parental factors (Figure 1; see the *Assessment Instruments* section). In addition, the researcher will also make a video recording of the parent and child playing in 3 play situations (child-led play [CLP], parent-led play [PLP], and clean up [CU]), which will consequently be coded using the Dyadic Parent-Child Interaction Coding System (DPICS) [52]. Following this, in phase B, the intervention phase starts. Depending on their random allocation, families will start off with PCIT with or without the VR element. Once again, they will electronically fill out the ECBI and OBVL-*kort* (OBVL-K) weekly, and they will also register their homework completion and (if applicable) their VR completion sheets. During the PCIT sessions, PCIT therapists will register the parental progress weekly by coding 5 minutes of playtime with the DPICS. Once families reach CDI completion, they will move on to phase C, which is the parent-directed interaction (PDI) phase of PCIT. Measurements in phase C are identical to those in phase B. After treatment completion, a posttreatment assessment will be performed, which will be identical to the pretreatment assessment. Phase D is the follow-up assessment, which takes place 6 months after treatment completion. The assessment is also identical to the pre- and posttreatment assessments (Figure 2; 10 CDI sessions and 6 PDI sessions are used as a random example).

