### Treatment

PCIT focuses on changing dysfunctional parent-child interactions in 2 phases and teaches authoritative parenting [17], which implies firm control, warmth to the parent-child relationship, and a balance between discipline and stimulating independence [53]. Therapists coach parents from behind a 1-way screen through an earpiece [17]. In the first phase of PCIT, which is the CDI phase, emphasis is placed on building up the quality of the parent-child relationship and increasing positive parenting skills. In addition, in this phase, children begin to build the ability to regulate their behavior [15]. This first phase lays the foundation for effective behavior change. In the CDI phase, parents follow their child’s lead in playing and are coached on using positive parenting skills, specifically, praise, reflective statements, behavioral descriptions, imitation, and enthusiasm [17]. The number of CDI sessions is dependent on the parents meeting the skill criteria (10 behavioral descriptions; 10 reflective statements; 10 labeled praises; and <3 questions, commands, or negative verbalizations during a 5-minute observation period).

However, the CDI phase alone is typically insufficient for children with disruptive behavior to return to displaying normal behavior [54]. After meeting the CDI skill criteria, the second phase of PCIT, which is the PDI, starts. The goal of the PDI phase is to further enhance the parents’ positive parenting skills to set consistent, predictable, and age-appropriate boundaries for their children [17]. In the PDI phase, parents are coached on using clear commands and how to apply consequences for compliance (praise) and noncompliance (timeout). In addition, they are taught and encouraged to keep using the positive parenting skills from the first phase. Once parents demonstrate achievement of skill criteria of both CDI and PDI skills, and their children’s behaviors according to the raw score on the ECBI Intensity Scale is <114, the treatment is completed, as standard protocol dictates [17].

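### The 15 families are to be preferably finishers, although completion is an outcome and 15 is also an attrition-inflated enrolment figure, so completion rate and completers' pre-post change are open to selection

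*Protocol article*

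**What the plan says.** All references are to the protocol article.

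- **Participants.** The target sample is given as "A total of 15 families will be included, preferably those who finish the treatment (including all treatment phases and measurement points"). The sample-size rationale repeats the preference: "this study will strive to include 15 families, preferably those who finish the entire trajectory". Among the reasons for 15 are a guideline under which "a minimum of 9 replicated single-case studies should be performed" and the wish to "compensate for the potential of a 40% attrition rate".
- **Aims.** One expectation is that "the overall completion of treatment will increase". Risk factors for dropout are also to be evaluated. The Discussion (Principal Findings) repeats that dropout should fall.
- **Inclusion Criteria.** The ECBI cutoff for entry is described as "meaning that all scores >131 will be included".
- **Treatment.** Once the CDI and PDI skill criteria are met and the child's "raw score on the ECBI Intensity Scale is <114, the treatment is completed".
- **Study Design.** Families are randomised, before the baseline phase, to a baseline length and to a VR start (at the start of CDI, or after 3 or 6 CDI sessions). The pretreatment assessment comes at the end of baseline. "After treatment completion, a posttreatment assessment will be performed", and follow-up takes place 6 months after completion. DPICS coding in session, ECBI and OBVL-K are weekly during treatment.

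**The concern.** A sample should be defined by what is known at entry. Here the stated preference concerns an event that lies after randomisation and that the study also wants to measure. If finishers are favoured, the completion rate no longer describes the families who started, and risk factors for dropout are studied in a sample from which dropouts have been thinned.

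The preference also touches the randomisation. A family allocated to VR after 6 CDI sessions may leave before receiving VR at all, so a preference for finishers can act differently across the VR start times. The Discussion intends to compare those timings at group level.

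A second layer comes from how completion is defined. It depends on parenting skills and on the ECBI, which measure the primary end point and a secondary one. Scores taken after completion come from families whose readings have already improved enough to meet the rule. A favourable pre-post change in that group is to be expected whatever VR contributes.

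**Working it through.** **1. Reproducing the 15.** Inputs from Participants: minimum 9 replications, attrition 40%.

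9 / (1 - 0.40) = 9 / 0.60 = 15.0

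This matches exactly, so the arithmetic belongs to 15 families enrolled, with 15 × 0.60 = 9 expected to finish and 15 × 0.40 = 6 expected to stop.

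**2. The other reading, 15 finishers.** At 40% attrition, 15 / 0.60 = 25 families would have to be enrolled. If only 15 are enrolled, and families finish independently, the chance that all finish is 0.60^15 = 0.0005. A sample of 15 finishers is therefore not reachable without extra enrolment, replacement or selection.

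**3. What happens to the completion rate.**

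- All enrolled families as denominator: expected 9/15 = 60%.
- Only finishers kept, or non-finishers replaced until there are 15: 15/15 = 100%, whatever the true rate.
- A partial preference gives a value in between, which the text does not allow one to determine.

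The Introduction gives 52% dropout for the same cited Dutch study. At that figure, expected completion is 48%, with 15 × 0.52 = 7.8 families stopping.

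**4. The ECBI thresholds.** Taking the cutoff above 131 as an entry requirement, and with whole-number scores, entry means at least 132 and the completion reading is at most 113. The fall between these two readings is at least 132 - 113 = 19 points. This is not the pre-post change. The pretreatment score is taken after a baseline of 4 to 6 weeks, and the posttreatment score is a separate administration after completion.

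**5. How much selection a separate posttreatment reading carries.** The documents give no means or SDs, so this is an illustration on assumed values: true mean 150, SD 20; screening above 131; reading-to-reading noise SD 8 or 12; true change varying between families with SD 15 or 25; no VR effect. Pretreatment and posttreatment are fresh readings. A completer is a family with a separate reading below 114.

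| Mean true change | Change, all families | Change, completers | Share completing | Completers with post below 114 |
|---|---|---|---|---|
| 0 | 0 | -20 to -38 | 3–9% | 42–73% |
| -15 | -15 | -30 to -45 | 12–20% | 57–79% |
| -30 | -30 | -40 to -52 | 31–36% | 69–84% |

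The excess in completers is 20 to 38, 15 to 30 and 10 to 22 points in the three rows. It shrinks as more families complete. All rows have far lower completion than the 60% implied by the plan, so the excess there would probably be smaller. If no family's true score changes, a fresh posttreatment reading shows no bias (mean change about 0). The direction is firm once true change varies between families. The size is not.

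**6. Skills.** The completion threshold of 10 + 10 + 10 = 30 positive verbalisations is coded by the therapist in session. The pre and post DPICS come from separate recordings of three play situations, and no baseline DPICS value is given. Selection runs in the same direction, but no minimum gain can be computed.

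**The case against.** The strongest reply is that the word preferably expresses a hope for retention. Finishing cannot be known at enrolment, the allowance for 40% attrition makes sense only if some of the 15 are lost, and an aim to study dropout needs families who drop out. This stands as the more plausible intention. It does not settle the text, which states the preference twice and lets one number serve both readings.

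Three stronger readings are tempting, and the article does not support them:

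- *That completion will be 100% by construction.* This needs replacement or omission of non-finishers, and no section states either.
- *That pre-post improvement is guaranteed, by at least 19 ECBI points or by reaching 30 skills.* The thresholds apply to the screening reading, the completion reading and in-session coding, not to the pre and post assessments.
- *That families who stop early get no posttreatment or follow-up score.* The article places these assessments after completion and says nothing about early stoppers. A full protocol may provide for them, and a condensed article is not at fault for leaving that out.

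It is also fair to say that the design's main comparison, within families around the introduction of VR, rests on weekly series that exist for families who later stop. The completion rule does not distort these, provided those families are analysed. Finally, the completion rule is standard PCIT practice rather than a sampling choice, and nothing here criticises it.

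**Conclusion.** The point holds in limited form. The Participants section gives two incompatible meanings to 15: families enrolled, of whom about 9 finish, and families who preferably finish. The completion denominator is therefore not fixed, and favouring finishers would bias completion upward, from an expected 60% (48% at the Introduction's dropout figure) to at most 100%. It would also condition on an event after randomisation.

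Separately, pre-post change in ECBI and skills among completers is selected toward improvement with or without VR, and cannot serve as evidence for VR. Its size cannot be derived from the documents. The illustration gives an excess of 10 to 38 ECBI points on assumed values with completion well below 60%, so it should be read for direction only. It also assumes that true change varies between families.

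The weekly DPICS, ECBI and OBVL-K comparisons are unaffected by the completion rule if early stoppers stay in the analysis. The change should be made, but it does not threaten the core of the design.

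**What to change.** - Delete the preference for finishers in both places in Participants. Define the 15 as families randomised, with dropouts not replaced. This agrees with 9/0.60 = 15.
- Use all randomised families as the denominator for completion and for the dropout analysis.
- Analyse the weekly DPICS, ECBI and OBVL-K of every randomised family up to the last observed week, and base conclusions about VR on these series.
- Label pre-to-post change in completers as descriptive.
- Optionally, invite families who stop early to the existing posttreatment and follow-up questionnaires. This would concern about 6 families at 40% attrition, or about 8 at 52%.

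The treatment completion rule stays as it is. The cost is wording, plus a handful of extra questionnaires if the optional step is taken. The drawback is a probably less favourable completion rate and pre-post result. The article reports 6 families enrolled at submission, so at that stage the definition could still be fixed for most of the sample.

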Worldwide, dropout rates vary between 12% and 67% [20], and specifically in the Netherlands, studies indicate that there is high attrition and that parents have a hard time grasping the different parenting skills. In that study, 52% of parents who received PCIT dropped out [19]. Attrition rates worldwide seem to be attributed to parenting stress levels and treatment barriers [20]. For instance, single parent status, problem severity of the child, and low socioeconomic status are often attributed to attrition. However, there remains some discrepancy in the literature on what factors contribute to families dropping out, although many studies have attempted to identify predictive factors [21-23]. Nonetheless, one study found that treatment completers reported significantly fewer child behavioral problems and less parental stress at follow-up than treatment dropouts [24]. This indicates that treatment should focus on making parents feel more confident in their parenting, thus potentially diminishing parenting stress and, with that, dropout rates. In further support, a study found that treatment completers showed increasing positive parenting skills and decreasing negative parenting skills from before to after treatment [21]. In addition, positive parenting skills appear to be crucial for improving the parent-child relationship [7]. A meta-analysis on PCIT showed that when meeting the skill criteria is required for completion of treatment, child externalizing behavior is significantly lower than when this is not a requirement [18]. However, when PCIT is offered in a shorter form in community samples (eg, the *standard* 12-session PCIT or the 8-session PCIT-Home), comparable effect sizes can still be yielded for a reduction in disruptive behavior [18,25]. Nonetheless, if skill criteria are met when taking the traditional PCIT protocol into account, PCIT has been shown to make impactful long-term improvements in parental warmth, responsiveness, and effectiveness [17]. In addition, studies have shown that the performance and motivation of a skill can be improved by deliberately practicing that skill [26]. Moreover, parenting programs that incorporate the opportunity to practice new skills with their children are considered more effective interventions than those that do not [27,28]. This suggests that it could be beneficial for parents to practice the skills they learn in the therapy more intensely, thereby potentially reducing dropouts and magnifying the scope of the treatment. It has previously been shown that with live coaching feedback, positive parenting skills increase rapidly, whereas negative parenting behavior decreases rapidly, especially early in the intervention. These results indicate that early interaction change in positive parenting skill acquisition is related to more positive child welfare outcomes [29]. In addition, research indicates that a current obstacle in PCIT is that parents may have a hard time grasping parenting skills, which leads them to drop out because of the inability to fully understand and translate the parenting skills to their home setting [19]. Therefore, to bridge the gap between practicing the (Praise, Reflect, Imitate, Describe, and Enthusiasm [PRIDE]) skills in therapy and applying the skills in a home setting, this study will implement a virtual reality (VR) element. VR allows parents to practice skills regardless of whether their child is home or awake, meaning that the ability to practice skills is on demand whenever they have their smartphone device near them. Over the past years, VR has become increasingly popular within the mental health care sector, as it creates opportunities that would otherwise not be possible [30]. Thus far, research has shown that using technology in PMT programs maintains positive treatment outcomes as long as therapist contact is maintained [31]. Specifically, within PCIT, previously implemented technology augmentations, such as Pocket-PCIT, have been shown to lead to increased treatment completion rates. This indicates a promising development in using technology innovations in an attempt to tackle similar barriers to treatment engagement [28].

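### The 15 families rest on 40% attrition from reference 19, but the Background reports 52% dropout from the same reference, and the two are not reconciled

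*Protocol article*

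**What the plan says.** The Participants section of the protocol article gives the reasoning for the sample size. It cites a What Works Clearinghouse (WWC) criterion that "the minimum number of participants necessary to demonstrate an intervention effect is 3 [41" and an American Psychological Association (APA) statement that "a minimum of 9 replicated single-case studies should be performed". It then reports that "attrition rates according to the standard PCIT ranged between 34% and 77% [43" and narrows this to the Dutch setting: "Specifically, in the Netherlands, a previous study showed a 40% attrition rate [19".

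From these it draws three purposes for 15 families: (1) to meet the WWC minimum of 3, (2) to be able to call the intervention effective under the APA guideline, and (3) to "compensate for the potential of a 40% attrition rate". On who is counted, it says: "A total of 15 families will be included, preferably those who finish the treatment (including all treatment phases and measurement points".

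The Background section, discussing attrition in the Netherlands, says: "In that study, 52% of parents who received PCIT dropped out [19". This is the same reference number that supports the 40%.

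**The concern.** One cited study is given two attrition rates, 12 percentage points apart, with no remark on why they differ. The Participants section sizes the study on the lower one.

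This is more than a slip in the literature review, because the 40% seems to produce the number 15. If the higher rate is the right one for families starting PCIT, the allowance for attrition is too small, and the expected number of finishers falls below the 9 that the plan links to a claim of effectiveness. What is at stake is the stated justification: whether purposes (2) and (3) can be asserted for 15 families. No endpoint, randomisation step, measurement or analysis depends on the figure.

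**Working it through.** **Inputs, all from the protocol article**

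- Families planned: 15 (Participants)
- Minimum replications cited from the APA: 9 (Participants)
- Minimum participants cited from the WWC: 3 (Participants)
- Attrition used for sizing: 40%, reference 19 (Participants)
- Dropout among parents who received PCIT: 52%, reference 19 (Background)
- Attrition range for standard PCIT: 34% to 77%, reference 43 (Participants)
- Worldwide dropout range: 12% to 67%, reference 20 (Background)

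**Step 1: reproduce the plan's figure.** Dividing the required number by the retained fraction gives 9/(1 − 0.40) = 9/0.60 = 15.0, an exact match. Multiplying up instead gives 9 × 1.40 = 12.6, rounded to 13, which does not match. The article does not print the formula, so the link is inferred from the exact match and from purposes (2) and (3).

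**Step 2: replace 40% with 52%.** Expected completers are 15 × (1 − 0.52) = 15 × 0.48 = 7.2. For scale, an expected 9 completers at this rate would correspond to 9/0.48 = 18.75, that is, 19 families.

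**Step 3: chance of reaching the thresholds.** Let X be the number of completers among 15 families, with attrition d and families dropping out independently. Then P(X ≥ m) = Σ C(15, k)(1 − d)^k d^(15 − k), summed over k = m to 15.

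| Attrition d | Source in the article | Expected completers, 15(1 − d) | P(X ≥ 9) | P(X ≥ 3) |
|---|---|---|---|---|
| 40% | Participants, ref. 19 | 9.0 | 0.610 | 0.9997 |
| 52% | Background, ref. 19 | 7.2 | 0.251 | 0.994 |
| 34% | Participants, ref. 43, low end | 9.9 | 0.781 | >0.999 |
| 77% | Participants, ref. 43, high end | 3.45 | 0.002 | 0.706 |
| 12% | Background, ref. 20, low end | 13.2 | 0.999 | >0.999 |
| 67% | Background, ref. 20, high end | 4.95 | 0.029 | 0.917 |

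The first two rows are the point at issue, because they come from one source. The other rows show that the quoted ranges are too wide to settle the matter: they run from near certainty of 9 completers to almost no chance.

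**Step 4: which rate fits this study as worded.** The Background describes the 52% as dropout among parents who received PCIT. The Participants section gives the 40% simply as that study's attrition rate. Every family included here is to receive PCIT-VR, so the 52% is described in terms at least as close to this population.

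**The case against.** **The two rates may measure different things.** The Background describes reference 19 as a randomized comparison of PCIT with family creative therapy. An overall attrition rate and a rate among PCIT recipients could both be correct, with different denominators or definitions. This stands as a possibility, and only the source can settle it. A reader might infer that the 40% is simply a mistake, or that 7 completers is now the expected outcome; the article supports neither. It shows two unexplained rates, and the shortfall holds only if 52% is the relevant one.

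**The article never says that 9 completers are required.** It speaks of 9 replicated single-case studies. A family that leaves during the parent-directed phase may already have supplied its comparison around the introduction of VR, which takes place in the child-directed phase (Study Design). Fewer than 9 completers therefore need not mean fewer than 9 analysable cases, and the 25% and 61% describe completers only. This also stands. However, the plan itself sizes on attrition and prefers families who finish, so it should say what it is counting.

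**The stated preference for finishers could mean 15 completers.** Purpose (3) would then have no function, since it treats 15 as the number before losses.

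**VR may lower dropout.** That is one of the study's own hypotheses (Aims), and the plan sizes on historical rates rather than on a hoped-for improvement.

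**An expected 9 is ordinary practice.** Agreed. Inflating to an expected number of completers is common, and no rule in the article demands a guaranteed probability. The 61% at 40% attrition is not in itself a defect.

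**Conclusion.** The point holds as an unreconciled inconsistency in a figure on which the sample size rests. The Participants section uses 40% and the Background reports 52%, both from reference 19. At 40%, 15 families give 9.0 expected completers and a 61% chance of at least 9. At 52%, they give 7.2 and 25%. If the higher rate applies, purposes (2) and (3) are not supported as stated. Purpose (1) is secure at either rate, with a chance of at least 3 completers above 99%.

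This rests on three assumptions: that 15 was derived as 9/(1 − 0.40), which is inferred but exact; that the 9 are counted as treatment completers; and that families drop out independently.

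A reader might go further and infer that the division is wrong, that the study is invalid, or that it must recruit 19 families. The article does not support this. The division is correct on its own input, no analysis depends on the rate, and families who drop out may still be analysable.

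**What to change.** In the Participants section:

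1. Check both rates against reference 19. Correct whichever is wrong or, if both are right, give the denominator of each and say which applies to families starting PCIT-VR.
2. Restate the justification with the resulting figures. If both rates remain plausible, for example: *15 families give an expected 7 to 9 treatment completers, with a 25% to 61% chance of at least 9, assuming independent dropout.*
3. Say whether the 9 replications are counted as treatment completers or as analysable cases. If analysable cases, the definition must suit every randomised VR start. A rule asking for several weekly DPICS scores before VR would exclude families allocated VR at the start of the child-directed phase, because the weekly baseline measures described in Study Design are the ECBI and the short OBVL, not the DPICS.
4. Align the Background sentence with the outcome.

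The cost is wording and possibly a less favourable stated figure. No extra families and no change to the design are needed.
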